## Abstract

**Background:**

Cancer-related fatigue (CRF) is one of the most common and distressing side effects of cancer and its treatment. During and after radiotherapy breast cancer patients often suffer from CRF which frequently impairs quality of life (QoL). Despite the high prevalence of CRF in breast cancer patients and the severe impact on the physical and emotional well-being, effective treatment methods are scarce.

Physical activity for breast cancer patients has been reported to decrease fatigue, to improve emotional well-being and to increase physical strength. The pathophysiological and molecular mechanisms of CRF and the molecular-biologic changes induced by exercise, however, are poorly understood.

In the BEST trial we aim to assess the effects of resistance training on fatigue, QoL and physical fitness as well as on molecular, immunological and inflammatory changes in breast cancer patients during adjuvant radiotherapy.

**Methods/design:**

The BEST study is a prospective randomized, controlled intervention trial investigating the effects of a 12-week supervised progressive resistance training compared to a 12-week supervised muscle relaxation training in 160 patients with breast cancer undergoing adjuvant radiotherapy. To determine the effect of exercise itself beyond potential psychosocial group effects, patients in the control group perform a group-based progressive muscle relaxation training. Main inclusion criterion is histologically confirmed breast cancer stage I-III after lumpectomy or mastectomy with indication for adjuvant radiotherapy. Main exclusion criteria are acute infectious diseases, severe neurological, musculosceletal or cardiorespiratory disorders. The primary endpoint is cancer-related fatigue; secondary endpoints include immunological and inflammatory parameters analyzed in peripheral blood, saliva and urine. In addition, QoL, depression, physical performance and cognitive capacity will be assessed.

**Discussion:**

The BEST study is the first randomized controlled trial comparing progressive resistance training with muscle relaxation training in breast cancer patients during adjuvant radiotherapy. Based on the analysis of physiological, immunological and inflammatory parameters it will contribute to a better understanding of the physiological and psychosocial effects and the biological mechanisms of resistance training. The ultimate goal is the implementation of optimized intervention programs to reduce fatigue, improve quality of life and potentially the prognosis after breast cancer.

**Trial registration:**

ClinicalTrials.gov NCT01468766

## Background

Adjuvant radiotherapy is used in more than 90% of all breast cancer patients. It is usually given after breast-conserving surgery and may be given after a mastectomy if patients are at high risk of recurrence. After breast-conserving surgery, adjuvant radiotherapy to the involved breast significantly increases the progression free survival and reduces the breast cancer death rate by about a sixth [1]. While radiotherapy reduces breast cancer recurrence and mortality it may also be associated with acute and long term toxicity. The most frequently reported adverse effect is cancer-related fatigue (CRF), a common early and also a late side-effect of irradiation, reported in up to 80% of patients during radiotherapy [2-6]. As per definition, CRF is a persistent, subjective sense of tiredness related to cancer or cancer treatment that interferes with usual functioning and that is usually not relieved with rest and is not related to an excessive amount of activity. Over the course of radiotherapy the proportion of patients with CRF and the severity of CRF gradually tends to intensify. CRF peaks at the end of radiotherapy and in about 30% of patients it may persist even for many months post-treatment [3,6-8]. Despite the high prevalence and the severe impact of CRF on the physical and emotional well-being and the quality of life (QoL), the aetiology of this common symptom and its correlates are poorly understood and effective treatment methods are scarce. Several interventions have been tested in the management of CRF. Although an optimal method has not yet been established, some promising results have been reported with relaxation therapy, group psychotherapy, physical exercise and sleep. The National Comprehensive Cancer Network (NCCN) guidelines recommend treatment for pain, emotional distress, and anemia as well as optimizing treatment for sleep dysfunction, nutritional deficiency or imbalance, and comorbidities [9]. Initially tested pharmaceuticals have shown severe adverse effects (e.g. erythropoietin), or did not show efficacy in phase III studies (e.g. methylphenidate) [10]. A Cochrane review from 2008, a roundtable of the American College of Sports Medicine published in 2010, and a recent comprehensive meta-analysis on published reports of 44 exercise studies with the endpoint CRF concluded that exercise may be an effective treatment method for CRF, but that the evidence is not yet convincing [11-13]. The meta-analysis published by Brown et al, however, was based on summary data from actual research papers but did not analyze individual patient data [13]. However, most of the previously reported controlled intervention trials used “usual care” as comparison group. Therefore, it is unclear to what extent the observed effects may be based on the physical exercise itself, or rather on psychosocial factors related to the group support or the attention by the trainer. Thus, methodologically correct studies are warranted to better define the causes, the optimal prevention and the management of CRF.

Furthermore, it is still unclear what type of exercise, i.e. aerobic or resistance training, and what point in time, i.e. during or after cancer treatment, is most effective. The majority of previous controlled trials investigated aerobic exercise. Resistance training has been little examined and even fewer studies tested resistance interventions performed during adjuvant radiotherapy [11,14,15].

The molecular mechanisms of fatigue as well as the molecular changes induced by exercise are still largely unknown. Inflammation and other immunomodulatory mechanisms are supposed to be of importance for the outcome and prognosis of cancer. Irradiation can cause a weakening of the immune system but may also induce severe systemic inflammation in the short, and perhaps even long-term [16-18]. Several large trials among healthy individuals or cancer survivors reported that exercise including resistance training can lead to a reduction of markers of inflammation such as C-reactive protein (CRP) [19-24]. These results suggest that anti-inflammatory factors might mediate the beneficial effects of resistance training on fatigue during adjuvant radiotherapy.

In addition, key immunomodulators like tumor-specific CD4^+^CD25^+^ forkhead transcription factor Fox P3 (FoxP3) positive regulatory T lymphocytes also known as regulatory T-cells (Tregs) are spontaneously induced by many types of cancer [25-27]. Increased levels of FoxP3-positive Tregs in peripheral blood and tumor have been reported in patients with various types of cancer including ovarian cancer [28,29], breast cancer [30] and other tumors [27]. A lack of FoxP3-expressing T-cells can lead to autoimmune disease, whereas an abundance of FoxP3-expressing regulatory T-cells can result in immune deficiency [25]. Increased numbers of Tregs have been associated with a worse breast cancer prognosis [31-33], For example, Bates et al. reported that high numbers of FoxP3-positive Tregs were identified in patients with ductal carcinoma in situ at increased risk of relapse, and in patients with invasive breast tumors with both shorter relapse-free and overall survival [30]. In addition to their potential value in predicting disease progression and relapse, FoxP3-positive Tregs have recently been reported to be a marker for the monitoring of therapeutic response. Merlo et al suggest that FoxP3 itself is expressed in breast cancer cells, and that the expression level is associated with patient survival [34]. Whereas increased numbers of Tregs have been correlated with a worse breast cancer prognosis [30-34], exercise has been correlated with a trend towards a better prognosis [35]. This raises the question whether exercise might have an effect on the level of Tregs and whether they might be one of the molecular mediators of the beneficial effects of exercise seen in cancer patients. To date, however, immunological and molecular factors have only been minimally studied with respect to fatigue, and the effect of resistance training during radiotherapy on the Treg level in breast cancer patients is unclear.

The aetiology of fatigue during radiotherapy is also not well defined. The course and severity differ between radiotherapy- and chemotherapy-induced fatigue, which suggest different pathways [36]. Overall, methodologically optimized randomized controlled clinical trials and a better understanding of the pathophysiology and the molecular mechanisms of fatigue induced by radiotherapy as well as the mode of action of resistance training are important for evidence-based exercise recommendations for breast cancer patients during treatment.

The BEST trial is a prospective, randomized controlled intervention study in breast cancer patients during adjuvant radiotherapy exploring the effects of a 12-week supervised progressive resistance training on CRF, QoL, depression, as well as muscular strength, cardiorespiratory fitness, and body composition. Moreover, pathophysiological, molecular and immunological mechanisms of fatigue and exercise will be analyzed.

To determine the specific effects of the exercise program itself beyond potential psychosocial effects related to a supervised group-based training, patients in the control group receive a comparable training schedule, yet with group-based progressive muscle relaxation (also called Jacobson’s progressive relaxation or Jacobson’s method) [37].

## Methods/design

### Study design

The BEST study (“Bewegung und Entspannung für Brustkrebspatientinnen unter Strahlentherapie”; English: “exercise and relaxation for breast cancer patients during radiotherapy”) is a prospective, randomized, controlled clinical intervention trial in stage I-III female breast cancer patients during adjuvant radiotherapy. Women have to provide written informed consent prior to participation in the study. After baseline assessments, participants are randomized to a supervised progressive resistance training or a supervised relaxation program over a period of 12 weeks (see Figure 1). Both interventions are administered group-based. Endpoints are assessed within 21 days before radiotherapy (baseline, T0), after the end of radiotherapy (week 7, T1), after the end of the intervention (week 13, T2), and 2, 6, and 12 months post-intervention (T3, T4, T5) (see Figure 2). Blood (serum, plasma, peripheral blood mononuclear cells (PBMCs)), urine, and saliva (5 samples over one day) are collected at T0, T1, and T2.

**Figure 1 F1:**

Study design of the BEST study.

**Figure 2 F2:**
[figure not shown]
Study flow of the BEST study.

To enhance the participation rate and maintain high compliance to the intervention scheme, participants are offered to train for another 12 weeks in the program of their choice after completion of the 12-weeks randomized intervention period. The intervention programs and several outcome measures are based on experiences from a randomized controlled trial with breast cancer patients during chemotherapy conducted by our group (BEATE study) [38].

The BEST study has been approved by the ethics committee of the University of Heidelberg in December 2010 (number S-447/2010) and is registered at ClinicalTrials.gov (http://NCT01468766).

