### Objectives

The primary objective of the BEST trial is to determine the effect of resistance training on fatigue compared to a relaxation control group among breast cancer patients during adjuvant radiotherapy.

Secondary objectives are to estimate the effects of the resistance training on quality of life, depression, cognitive function, and early and late radiotoxicity, as well as on physical fitness, including muscle strength, cardio-respiratory fitness, flexibility, and body composition. The effects of the resistance training on immunologic and inflammatory parameters and other biomarkers relevant to cancer prognosis will also be tested. Further, hypothesized biological mediators of physical activity and cancer-related fatigue will be explored and the relationships between cancer-related fatigue, physical fitness, and biomarkers of stress, inflammation, and immune function will be modelled. Safety and feasibility of progressive resistance training during radiotherapy will be evaluated, and the sustainability of the effects will be assessed.

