### Data analysis

The main intervention effect will be assessed on the basis of a comparison between exercisers and controls as defined at randomization, regardless of exercise adherence, i.e. according to the intent-to-treat principle. The differences in fatigue between groups will be assessed with a generalized estimating equation (GEE), which accounts for repeated observations on the same subjects over time. This method provides the most efficient estimate for the intervention effect in pretest-posttest trials [61]. Normality assumptions will be checked and data if necessary transformed. Imputation-based sensitivity analyses will be conducted to examine the potential effect of missing data on the results.

Similar analyses as for fatigue will also be performed for the secondary endpoints. In addition, analyses will be performed stratified by pre-treatment (e.g. neoadjuvant, adjuvant or no previous chemotherapy), to evaluate potential differential effects of the exercise intervention by pre-treatment. Further, subgroup effects of resistance training versus relaxation controls will be explored stratified by training adherence, changes in muscle strength, cardiorespiratory fitness, and body composition. Correlation analyses will be used to examine the relationship between changes of the various measured endpoints. Regression analyses regarding the repeated measurement design (T0, T1, T2, T3, T4, T5) will be applied to investigate the association between therapy modalities, cardiorespiratory fitness, muscle strength, and body composition and the different fatigue as well as QoL dimensions. The influence of other potential confounding factors, such as age, smoking, clinicopathologic characteristics, and comorbidities will be explored and accounted for in the analyses.

In addition, change in physical activity behavior post intervention will be explored for the follow-up time points using descriptive analysis.

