## Discussion

The BEST study will add to current knowledge about exercise in breast cancer patients with respect to several novel aspects being tested: (1) Exercise performed in parallel to radiotherapy; (2) progressive resistance training; (3) exercise effect beyond psychosocial training effects; (4) effects on immune function, and (5) sustainability and long-term effects of a 12-week exercise intervention.

Among breast cancer patients receiving radiotherapy the most frequently reported side effect is fatigue. As about 72.000 women in Germany are newly diagnosed with breast cancer each year [62], the majority receiving radiotherapy, this radiation-related fatigue is a substantial health problem. Exercise may be an effective treatment against fatigue. Thus, it is surprising that exercise during radiotherapy has been minimally investigated in breast cancer patients so far. To our knowledge, only five randomized exercise trials included breast cancer patients during adjuvant radiotherapy [63-67]. Three of these studies included also patients during other adjuvant treatments (chemotherapy, hormone therapy) [64,66,67] and one was a pilot study including also prostate cancer patients [65], leaving only one exercise study with only breast cancer patients during adjuvant radiotherapy but with a small sample size of only n=46 [63].

Radiation can be muscle damaging (myotoxic), resulting in significant reductions in skeletal muscle mass and function [68]. Resistance training can counteract this muscle degradation. The negative influence of cancer therapy is a major rationale to investigate the effect of resistance exercise during adjuvant radiotherapy, as training in parallel to adjuvant treatment might prevent or mitigate treatment side effects such as fatigue.

Previous randomized exercise trials mostly investigated aerobic exercise, but benefits of resistance training in cancer patients and survivors on quality of life and fatigue have also been reported [15,69-71]. To our knowledge, only seven studies investigated pure resistance training in cancer patients and survivors [69,72-77]. Among those studies, two had insufficient power (n=22 and 38) [76,77] and of the others only three focused on breast cancer patients [69,72,75]. However, no randomized controlled trial investigated progressive resistance training in breast cancer patients during adjuvant radiotherapy.

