A further strength of the BEST study is the choice of the control group, i.e. of a standardized relaxation training without any aerobic or resistance exercise components, but which reflects the training schedule and psychosocial conditions of the exercise intervention. Positive psychosocial “side effects” of group-based exercise training have been observed [78], which potentially can contribute to a lower perception of fatigue and higher QoL, in addition to physiological effects of the exercise on fatigue. Thus, the BEST design enables us to discern the “pure” physiological effects of exercise beyond potential psychosocial effects of a group-based training, which are related to social interactions, group support, improved self-efficacy, or attention by the trainer. Psychosocial and behavioural interventions have also shown some beneficial effects regarding fatigue and QoL [79,80]. Thus, it is still unclear, to what extent the observed benefits of exercise interventions are really caused by physical training, because previous studies have commonly used a “usual care” control group.

Further, the pathophysiology of fatigue and the mode of action of exercise on its prevention and treatment are not well understood. Our trial enables investigation of the effects of resistance training on immunologic parameters as well as on biomarkers of inflammation, oxidative stress, and diurnal cortisol slopes. While the intervention effect on fatigue and potential underlying biological mediators is one focus of the trial, another focus is the examination of the effects of resistance exercise on prognostic factors and health-relevant biomarkers. Especially regulatory T-cells will be investigated in detail, as those have been found to be associated with prognosis in breast cancer patients [31-33].

Finally, in case of the detection of beneficial effects during or at the end of an exercise intervention, it is of interest whether those benefits sustain over a longer period of time. To-date, data on the sustainability of exercise interventions is limited. Therefore, we follow the BEST participants over one year post-intervention and assess at 3 post-intervention time-points fatigue, QoL, physical fitness, and their physical activity behavior.

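### Both arms may train another 12 weeks in a programme of their choice, so the T3–T5 comparison does not isolate the sustainability of the 12-week randomised intervention

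*Protocol article*

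**What the plan says.** - **Randomised period** (Study design): "participants are randomized to a supervised progressive resistance training or a supervised relaxation program over a period of 12 weeks".
- **Extension** (Study design, paragraph after Figure 2): "participants are offered to train for another 12 weeks in the program of their choice after completion of the 12-weeks randomized intervention period". The stated purpose is to raise participation and keep compliance high. Neither arm is excluded and neither programme is ruled out.
- **Visits** (Study design): assessments take place "after the end of the intervention (week 13, T2), and 2, 6, and 12 months post-intervention (T3, T4, T5").
- **Objective** (Objectives, last sentence): "the sustainability of the effects will be assessed".
- **Claim** (Discussion, list of novel aspects): "sustainability and long-term effects of a 12-week exercise intervention". Later in the Discussion, sustainability is the reason given for the long follow-up: "we follow the BEST participants over one year post-intervention and assess at 3 post-intervention time-points fatigue, QoL, physical fitness".
- **Analysis** (Data analysis): the main effect is a "comparison between exercisers and controls as defined at randomization, regardless of exercise adherence, i.e. according to the intent-to-treat principle", with similar analyses for the secondary endpoints. Physical activity after the intervention is explored descriptively. The article does not connect the extension with the reading of T3–T5.

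**The concern.** Until week 13 the arms differ by design only in the randomised programme. After that, a relaxation patient may start resistance training and a resistance patient may carry on with it. From T3 onwards the arms can therefore differ both in the first 12 weeks and in what participants chose to do in the next 12.

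This leaves the long-term results open to two readings. If the arms do not differ at T3–T5, the benefit may have faded, or controls may have caught up by training. If they do differ, the benefit may have lasted, or exercisers may simply have continued. The two distortions run in opposite directions, so the contrast cannot be called conservative. At stake is a stated secondary objective and one of the five aspects that the article presents as novel.

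**Working it through.** **1. The plan's own figure.** Sample size section: standardised effect 0.5, two-sided t-test, significance level 0.05, power 80%, drop-out at most 20%. The exact t-test needs 64 per arm, and 64 / (1 − 0.20) = 80 per arm, or 160 in total. The stated number reproduces; power with 64 per arm is 0.801. This calculation concerns the change from baseline to week 13 only. The article claims no power for T3–T5.

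**2. Timeline.** Inputs: randomised period 12 weeks, extension 12 weeks, visits 2, 6 and 12 months post-intervention. One month = 365.25 / 12 / 7 = 4.348 weeks. Assumption: the extension starts directly after week 12, so it ends at week 12 + 12 = 24.

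| Visit | Week = 12 + months × 4.348 | Relative to week 24 |
|---|---|---|
| T3 | 12 + 8.7 = 20.7 | 3.3 weeks before the extension ends |
| T4 | 12 + 26.1 = 38.1 | 14.1 weeks (3.2 months) after it ends |
| T5 | 12 + 52.2 = 64.2 | 40.2 weeks (9.2 months) after it ends |

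Counting from week 13 moves every date by one week and leaves the gaps unchanged. T3 is 8.7 weeks after the randomised period, so it falls inside the extension for any start delay shorter than that.

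**3. Possible training histories.**

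| Randomised to | Chooses | Weeks of supervised resistance training by week 24 |
|---|---|---|
| Resistance | Resistance | 12 + 12 = 24 |
| Resistance | Relaxation or nothing | 12 |
| Relaxation | Resistance | 0 + 12 = 12 |
| Relaxation | Relaxation or nothing | 0 |

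The second and third rows have the same amount of resistance training but sit in opposite arms.

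**4. What the contrast contains.** Let *D* be the difference at a later visit had nobody extended, *p* the share of exercisers who continue with resistance training and *g* their mean extra gain, and *q* the share of controls who take it up and *h* their mean gain. Ignoring any effect of choosing relaxation in the extension, the observed contrast is

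*D* + *p·g* − *q·h*.

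Sustainability of the 12-week programme is *D*. The article reports no plan to present *p* or *q*, and *D* cannot be recovered from the contrast alone.

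**5. Illustration of one direction only.** Assume *D* = 0.5, *p·g* = 0 and *h* = 0.5, with 64 per arm. The contrast is then 0.5 × (1 − *q*). None of these values for T3 is in the documents.

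| *q* | Contrast (SD) | Power, two-sided 0.05 |
|---|---|---|
| 0% | 0.50 | 0.80 |
| 20% | 0.40 | 0.61 |
| 30% | 0.35 | 0.50 |
| 40% | 0.30 | 0.39 |
| 50% | 0.25 | 0.29 |

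Continuation by exercisers (*p·g* > 0) would push the contrast the other way.

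**The case against.** **The primary result is not at risk.** This stands. The primary endpoint is measured at week 13, and the extension comes after the randomised period. A reader might infer that the extension contaminates the primary model because fatigue is also collected at T3–T5. The Data analysis section does not support that. It presents the fatigue GEE as a method for pretest–posttest trials without naming T3–T5 in it. The list T0 to T5 belongs to separate regressions on therapy modalities, fitness, strength and body composition.

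**The long-term comparison is still randomised.** This also stands. A reader might infer that the T3–T5 contrasts are worthless. They are not: they validly compare the two randomised starts, each followed by free choice. The limit is on what may be attributed to the 12 weeks alone.

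**Later behaviour is partly covered.** Table 2 records physical activity at T2 to T5, and the repeated-measures regressions run to T5. This helps description, but the recorded items are walking, cycling and sports, and neither analysis is said to use extension uptake or programme choice.

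**Timing, uptake and recording may be settled elsewhere.** No start date for the extension is given, the study-flow figure is not shown, and a full protocol may provide for recording. So T3 falling inside the extension rests on an assumption, and missing recording detail is not in itself a fault. What remains is visible in the article: it makes the offer and also claims sustainability of a 12-week intervention.

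**The power figures are hypothetical.** This stands. They suppose that the full effect would otherwise persist and that switching controls gain all of it, although T3 may come before their 12 weeks are over.

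**Conclusion.** The concern holds as a mismatch between design and claim for a secondary objective. As written, the plan would credit to the 12 randomised weeks a T3–T5 difference that also reflects crossover and continued training. The direction of the distortion is not fixed. Its size depends on uptake, which the documents do not give, so the illustrative figures do not measure this trial's problem.

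The conclusion on T3 assumes that the extension starts at once, or within about 8.7 weeks. The broader conclusion, that T3–T5 do not isolate the effect of the 12 weeks, needs only that some participants accept the offer in a way that changes their later outcomes. The primary endpoint and the sample size stand, provided T2 is assessed before extension training begins.

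**What to change.** 1. Define and label the T3–T5 contrast as the effect of 12 randomised weeks followed by an optional, self-chosen 12-week programme.
2. In the Objectives and Discussion, replace the claim of sustainability of a 12-week intervention with wording that matches this contrast.
3. Record, or retrieve where records exist, the programme chosen and the sessions attended in the extension, and report uptake by arm beside the T3–T5 results. The Interventions section describes attendance records for the randomised programme; whether they cover the extension has to be confirmed.
4. State that T2 is assessed before any extension training starts, and when the extension starts relative to T3.

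An analysis that adjusts for extension training is optional and supportive only. It would need assumptions about who chooses to extend, and with high uptake in 160 women few participants might remain without extension training.

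The cost is a change of wording, a narrower long-term claim and some data retrieval. Recruitment ended in March 2013, so for many participants retrieval may be the only option and may be incomplete. The extension offer itself need not change.
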